#### Intervention arm (taVNS)

2.6.2

In addition to standard care, participants randomized to the intervention arm will receive taVNS delivered using a Huatuo SDZ-IIB electronic acupuncture stimulator (see Figure 2). Procedures are as follows:

**Figure 2 F2:**
[figure not shown]
Device and stimulation sites. Both groups used the HuaTuo SDZ-IIB device with identical parameters. Red dots indicate taVNS sites: CO7 (large intestine point) and CO13 (spleen point) in the cymba conchae. Blue dots indicate sham sites: SF2 (wrist point) and SF4 (shoulder point) in the scapha.

Stimulation site: auricular regions with high density of auricular branch vagus nerve (ABVN) fibers—specifically the cymba conchae and cavum conchae—targeting auricular “Large Intestine Point” (CO7) and “Spleen Point” (CO13) points as anatomical targets for modulation of gastrointestinal function.

Preparation: prior to each stimulation session, trained personnel will disinfect the skin, place and secure electrodes over the marked sites, and verify electrode impedance and device function.

Stimulation parameters: intermittent stimulation with an on/off cycle of 2 s on/3 s off; pulse width of 0.5 ms; frequency approximately 25 Hz; and current intensity individualized within the range 0.5–1.5 mA, titrated to achieve a mild tingling or warm sensation without pain. Intensity will be adjusted according to participant tolerance. This treatment protocol is based on a multicenter randomized controlled trial protocol validated for gastrointestinal disorders (Zhu et al., 2021; Shi et al., 2024; Yin, 2025). Furthermore, evidence from Molefi et al. (2025), which examined healthy subjects with visual-induced motion sickness and found that a 20 Hz frequency combined with a 0.2 ms pulse width did not significantly improve the composite gastrointestinal symptom score, further supporting the rationale for our choice of parameters.

Adverse sensations: if a participant experiences notable discomfort during stimulation, the intensity will be reduced or the session terminated and the event recorded as an adverse event (AE).

Detailed session duration and scheduling will follow the study protocol (see Figure 2 and the procedure manual), and all interventions will be administered by personnel trained in taVNS application.

#### Control arm (sham)

2.6.3

The control arm will receive a sham stimulation designed to control for non-specific effects of device application and patient interaction while avoiding stimulation of vagal auricular sites. Procedures mirror those of the intervention arm with the following distinctions:

Stimulation site: electrodes will be placed on the scapha (non-vagal area), targeting auricular “Shoulder Point” (SF4) and “Wrist Point” (SF2) points that are not anatomically associated with ABVN or gastrointestinal vagal pathways, ensuring no anatomical overlap with the active taVNS targets (Peuker and Filler, 2002).

Device and procedures: the identical Huatuo SDZ-IIB device model, electrode preparation, disinfection, participant positioning, and nominal stimulation parameter settings (pulse pattern, frequency, and nominal current range) will be used to preserve blinding. The only intentional difference is the stimulation target (site); internal device output routing will be arranged so that the sham site receives a non-vagal stimulation pattern while maintaining similar sensation characteristics.

This sham control procedure is intended to preserve participant blinding and to isolate the specific effects of auricular vagal stimulation.

Notes on safety and documentation.

All interventions, device settings, session timing, and any deviations will be documented in the case report form (CRF). Adverse events will be recorded and managed according to the protocol's safety monitoring plan and reported to the DMC and ethics committee per predefined timelines.

#### Treatment schedule and operational management

2.6.4

All participants will receive two stimulation sessions per day (morning and evening), each lasting 30 min, on 5 consecutive weekdays (Monday–Friday) for 2 consecutive weeks (total 10 sessions). During the initial treatment phase, the first three sessions will be administered and supervised in hospital outpatient or inpatient settings by trained study personnel; these sessions also serve as hands-on training for participants who will continue treatment at home. Thereafter, participants may complete remaining sessions at home according to the training protocol.

Home-based treatment requires daily completion of a treatment log documenting treatment time, device current intensity, local sensations, and any gastrointestinal symptoms. Study staff will review logs and confirm adherence weekly by telephone or via a secure remote platform, and will address participant queries. All interventions and any medication adjustments will be performed according to standard operating procedures (SOPs), recorded contemporaneously, and entered into the case report form (CRF).

Any deviation from the prescribed stimulation parameters or protocol procedures must be recorded with rationale. All staff administering or supervising treatments will be trained and certified according to the study training curriculum; competency assessments will be documented.

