### Sample size justification

2.4

Sample size for this randomized, sham-controlled pilot and feasibility trial was determined in full alignment with the CONSORT 2010 Statement: Extension to Randomized Pilot and Feasibility Trials (Eldridge et al., 2016), and the optimized sample size estimation method for pilot trials with continuous primary outcomes established by Whitehead et al (Whitehead et al., 2016). As an external pilot trial, the core aim of sample size setting is not to power formal hypothesis testing for intervention efficacy, but to generate a sufficiently precise estimate of the standard deviation of our primary outcome (Metformin Symptom Severity Score total score) to inform the design of a future definitive randomized controlled trial. In detail, according to the optimized sample size estimation method for pilot trials established by Whitehead et al., an estimated final sample of 25 evaluable participants per group (after accounting for a 15% attrition rate from the 30 enrolled participants) yields 48 degrees of freedom for variance estimation. This well exceeds the minimum threshold of 20 degrees of freedom recommended in the literature for stable, unbiased variance estimation in pilot research. No formal hypothesis testing for intervention efficacy is planned in this pilot trial. Core feasibility endpoints include: recruitment rate (target ≥8 participants per month), screening failure rate, treatment adherence rate (defined as completing ≥80% of scheduled treatment sessions), attrition rate (estimated at 15% based on published neuromodulation trials in patients with T2DM), and protocol violation rate. Accounting for a 15% attrition rate, the final enrollment target is 60 participants (30 per group) (Whitehead et al., 2016).

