### Interventions

2.6

This is a parallel-group trial employing a “standard care + targeted intervention” design. Both groups will receive standardized diabetes management and metformin therapy as background treatment; in addition, participants will receive either taVNS or sham control group. The treatment course for both arms is 2 weeks, with subsequent follow-up assessments.

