### Statistical methods

2.10

All data will be managed according to GCP guidelines for clinical trials. Two independent researchers will perform double data entry for all variables, including bowel urgency scores, glucose and insulin metabolism markers, serum inflammatory markers, and safety parameters. Cross-verification is mandatory, and the database will be locked without authorization.

Statistical analyses will be performed by blinded biostatisticians using SAS 9.4 and R 4.2.1. Two analysis sets will be applied: the intention-to-treat (ITT) set includes all randomized participants, and the per-protocol (PP) set includes participants completing ≥80% of the treatment course without major protocol violations, for sensitivity analysis.

Baseline characteristics will be summarized by group. Continuous variables are assessed for normality using the Shapiro–Wilk test: normally distributed variables are presented as mean ± SD, non-normal as median [IQR]; variance homogeneity is assessed via Levene's test. Categorical variables are expressed as counts (*n*) and percentages (%). Between-group comparisons: independent *t*-test or Mann–Whitney *U*-test for continuous variables, Pearson χ^2^ or Fisher's exact test for categorical variables.

Primary and continuous outcome variables (bowel urgency score, FBG, PG2h, FINS, C-peptide, HOMA-IR, ISI, GA, serum IL-6/IL-10/TNF-α, GLP-1, 5-HT, D-lactate, diamine oxidase, and fecal bile acids) will be analyzed using linear mixed-effects models (fixed effects: group, time, interaction; random effect: participant), reporting least-squares means with 95% *CI*. The exact mathematical formulas and covariance structures for these linear mixed-effects models will be fully reported in the final trial publication. Categorical outcomes are analyzed via χ^2^ or Fisher's exact test.

A Multiple Imputation (MI) model will be used as the primary method for missing data. The imputation model will include all primary and secondary outcomes, plus baseline covariates (age, sex, duration of diabetes, baseline metformin dose, baseline Metformin Symptom Severity Score score), with 20 Markov Chain Monte Carlo iterations to generate 20 imputed datasets. The pre-specified linear mixed-effects model will be performed on each dataset, with results pooled via Rubin's rules (Heymans and Twisk, 2022).

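### Section 2.6.4 schedules 20 stimulation sessions but states a total of 10, so the 80% adherence cut could be read as 16 of 20 or 8 of 10

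*Protocol article*

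**What the plan says.** Section 2.6.4 (Treatment schedule and operational management) sets the regimen for both arms in one sentence: "two stimulation sessions per day (morning and evening), each lasting 30 min, on 5 consecutive weekdays (Monday–Friday) for 2 consecutive weeks (total 10 sessions". The first three sessions are supervised at the hospital and the rest may be done at home. For the home phase, "Home-based treatment requires daily completion of a treatment log", and "Study staff will review logs and confirm adherence weekly by telephone or via a secure remote platform".

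Section 2.4 (Sample size justification) lists among the core feasibility endpoints the "treatment adherence rate (defined as completing ≥80% of scheduled treatment sessions". Section 2.10 (Statistical methods) says that "the per-protocol (PP) set includes participants completing ≥80% of the treatment course without major protocol violations". Section 2.6 (Interventions) uses the term treatment course for the period: "The treatment course for both arms is 2 weeks, with subsequent follow-up assessments".

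Section 2.6.2 adds: "Detailed session duration and scheduling will follow the study protocol (see Figure 2 and the procedure manual". The manual is not available here, and the caption of Figure 2 describes only the device and the stimulation sites. No other section shown gives a total number of sessions.

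**The concern.** The frequency, the number of days and the number of weeks in the sentence do not multiply to the total it gives; they differ by a factor of two. The sentence uses session for each 30-minute morning or evening application, so the total cannot be read as a count of something else without changing the meaning of the word halfway through.

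Two things depend on the count. The first is the prescribed dose, which a reader who wants to repeat the regimen or design the confirmatory trial has to take from this section. The second is the denominator of the adherence rate. Section 2.4 says that the trial is not powered for efficacy and that feasibility endpoints are central, so the adherence rate is one of the main results the pilot will report. Most sessions may take place at home (17 of 20, or 7 of 10, after the three supervised ones), and staff confirm adherence from participants' logs. They need one agreed number to score against.

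**Working it through.** **Inputs**, all from section 2.6.4 unless noted:

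- sessions per day: 2 (morning and evening)
- treatment days per week: 5
- weeks: 2 (also in section 2.6)
- minutes per session: 30
- stated total: 10 sessions
- adherence cut: at least 80% of scheduled sessions (section 2.4)

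**Step 1: try to reproduce the stated total.** Sessions = sessions per day × days per week × weeks = 2 × 5 × 2 = 20. The stated 10 is not reproduced.

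**Step 2: look for a reading that gives 10.**

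- Once daily: 1 × 5 × 2 = 10, which contradicts two sessions a day.
- One week only: 2 × 5 × 1 = 10, which contradicts two weeks.
- Treatment days: 5 × 2 = 10, which is a count of days, not of sessions.

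The third is the likeliest origin. None agrees with the sentence as written.

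**Step 3: carry both totals forward.**

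| | Total of 20 | Total of 10 |
|---|---|---|
| Stimulation time | 20 × 30 = 600 min | 10 × 30 = 300 min |
| Adherence cut | 0.8 × 20 = 16 sessions | 0.8 × 10 = 8 sessions |

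**Step 4: when a participant would be misclassified.** If delivery and scoring both use 20, or both use 10, nobody is misclassified. The problem arises only if treatment is delivered twice daily and scored against 10. The cut is then 8 sessions, and 8/20 = 40% of the delivered schedule counts as adherent where the definition intends 80%.

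**Step 5: the per-protocol set.** This cut refers to the treatment course, not to sessions, so it may count days or sessions. If it counts days, and if a day counts once at least one session is done (an assumption; the article does not say), then 0.8 × 10 = 8 days is enough. That corresponds to anything from 8 × 1 = 8 to 8 × 2 = 16 sessions, or 40% to 80% of 20.

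**The case against.** The strongest reply is that the schedule is spelled out in full and only the bracketed summary is wrong. A careful reader would take 20 as the number of scheduled sessions, and section 2.4 refers to scheduled sessions rather than to a fixed 10, so the cut is 16. If the trial is really once daily, 8 of 10 is correct and again nobody is misclassified. The harmful combination is also easy to notice: a fully compliant participant would score 20/10 = 200%. Home logs and case report forms record session timing, so sessions could be recounted whatever the bracket says. The procedure manual may already hold the right number.

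Much of this stands, and it limits the consequence. The 40% figure is a worst case under one specific error, not an expected effect. The source data should allow a correct count. How the per-protocol set counts its 80% is a detail that an article can leave to a fuller document; it would not be a finding on its own, and that set serves only a sensitivity analysis.

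It does not remove the error. The article does not leave the total to another document; it states one, and that total contradicts the schedule beside it. Preferring 20 is a sensible inference, but the text shown does not settle it, and the choice changes both the stated dose and the denominator of a core endpoint.

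**Conclusion.** The sentence is wrong as written: its schedule gives 20 sessions and its total says 10. The arithmetic is certain. That 20 is the intended number is probable, not established. The discrepancy is a factor of two in the stated dose (600 against 300 minutes, in both arms) and in the adherence cut (16 against 8 sessions).

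An effect on the reported adherence rate is conditional on delivery on the 20-session schedule and scoring against 10. The intention-to-treat estimate, the between-arm comparison and the sample size of 30 per group do not depend on the session count. It should be fixed, because it concerns the denominator of a core feasibility endpoint, but it does not threaten the trial's validity.

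**What to change.** - **Section 2.6.4:** change the total to 20 sessions over 10 treatment days. If 10 sessions are intended, change the frequency to once daily instead.
- **Section 2.4:** state the adherence cut as a count: at least 16 of 20 sessions, or 8 of 10 if once daily.
- **Section 2.10:** add a clause saying whether the per-protocol threshold uses the same session count.
- Check that the procedure manual, the treatment log and the case report form carry the same total before adherence is scored.

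The cost is one number, one count and one clause. If twice daily is intended, no patients, visits or procedures are added. If once daily is intended, the stated frequency changes.

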#### Observation schedule and sample handling

2.6.5

The overall observation period is 5 weeks, comprising a 1-week baseline period (Week −1 to 0), a 2-week treatment period (Weeks 0–2), and a 2-week follow-up period (Weeks 2–4). Primary and key secondary outcomes (Metformin Symptom Severity Score, Bristol Stool Form Scale, and bowel urgency) as well as glycaemic/metabolic indices and selected inflammatory and mechanistic biomarkers will be assessed at baseline, Week 2, and Week 4. Selected biochemical markers will be repeated at baseline and either Week 2 or Week 4 according to the prespecified sampling schedule in the protocol appendix.

All biological specimen collection, processing, transport, and storage will follow a unified SOP. Blood samples will be drawn after an overnight fast unless otherwise specified, kept short-term at 4 °C, and transferred to long-term storage at −80 °C within the time limits defined in the SOP. Laboratory assay methods, quality-control procedures, and batch management are described in the trial appendix. The timeline of interventions, assessments, and visit windows is detailed in Table 1; adverse-event monitoring will be continuous throughout the entire study period.

**Table 1 T1:** Treatment and data collection.

Category	Study phase	Baseline	Visit 1	Visit 2
	Visit window	(Day 0)	Week 2	Week 4
Information collection	Basic medical history collection	×		
	Informed consent obtained	×		
	General demographics collection	×		
	Past medical and treatment history	×		
	Comorbidities and treatment history	×		
	Eligibility criteria check	×		
Primary outcomes	Metformin symptom severity score	×	×	×
Secondary outcomes	Bristol stool form scale	×	×	×
	Defecation urgency	×	×	×
	Quality of life scale	×	×	×
	FBG	×	×	×
	PG2h	×	×	×
	GA	×	×	
	IL-6, IL-10, TNF-α		×	
	GLP-1, BA, 5-HT, D-LA		×	
	ALT, AST, BUN, Cr (liver and renal function)		×	
Sample and data management	Adverse events (AEs) monitoring		×	×
	Sample collection record		×	
	CRF review by investigator (CRF-PI)	×	×	×
	CRF review by monitor (CRF-MON)	×	×	×
	Blinding assessment		×	×

“ × ” indicates that the corresponding assessment is performed at that visit. Baseline = day 0; visit 1 = week 2 (±3 days); visit 2 = week 4 (±3 days). All blood and stool specimens will be collected after an overnight fast.

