### Randomization and blinding

2.5

Participants will be randomized 1:1 to taVNS group or sham control group, with stratification by age and gender to balance baseline characteristics between groups. The randomization sequence will be generated by an independent third-party biostatistician using SPSS 26.0, with group allocation sealed in sequentially numbered, opaque envelopes for strict allocation concealment. After baseline assessment, a dedicated study coordinator (fully blinded to group assignment) will open envelopes in numerical order to assign eligible participants.

Given the anatomical specificity of active and sham stimulation sites, intervention staff responsible for electrode placement and device operation cannot be blinded to group allocation. To mitigate potential bias, we have implemented pre-specified rigorous safeguards: The blinded coordinator exclusively manages group allocation, and only provides intervention staff with pre-marked anatomical diagrams of stimulation sites, with no disclosure of group identity at any time. Non-blinded intervention staff are strictly barred from outcome assessment, data entry, statistical analysis, or any communication with participants about group allocation or expected intervention effects. Both groups use identical stimulators with consistent nominal parameters; all intervention staff receive centralized standardized training to ensure identical operational execution and participant interaction across groups.

All outcome assessors, data analysts, biostatisticians, and participants will remain fully blinded to group allocation throughout the trial. Furthermore, treating physicians are solely responsible for routine clinical management and safety assessments; they have no access to group allocation and are strictly isolated from intervention implementation and outcome assessment. Participants will be informed that both interventions may induce a mild tingling sensation, and subjective feeling cannot be used to infer group assignment, to minimize anticipation bias. Outcome assessors will receive standardized training and regular inter-rater reliability checks to reduce measurement bias.

The effectiveness of the blinding will be formally assessed in Weeks 2 and 4 using the validated James Blinding Index (BI) method (James et al., 1996). The detailed statistical procedures for this assessment are outlined in the “Statistical Methods” section.

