#### Primary efficacy outcome and assessment time points

2.7.2

The primary efficacy endpoint is the total score of the Metformin Symptom Severity Score, a validated, widely used self-report tool originally developed and psychometrically validated by McCreight et al. specifically for evaluating metformin-related gastrointestinal intolerance in adults with T2DM (McCreight et al., 2018).

In the original validation study by McCreight et al., this questionnaire demonstrated excellent reliability and validity: it showed strong internal consistency (Cronbach's α > 0.8), good test-retest reliability, and significant discriminant validity, with a highly significant difference in total scores between metformin-intolerant and metformin-tolerant patients (*P* < 0.0001) (McCreight et al., 2018). The questionnaire covers medication adherence, reasons for discontinuation, dose tolerance, gastrointestinal symptoms (nausea, abdominal bloating/pain, and diarrhea; frequency and subjective severity), changes in baseline symptoms, and an overall subjective tolerance rating, with a total score ranging from 0 to 50 points (0–10 = tolerable, 11–20 = mild intolerance, 21–30 = intolerable, 31–50 = severe intolerance). This questionnaire is used for the quantitative assessment of intolerance-related symptoms in this trial, not as a basis for clinical diagnosis.

Assessment time points include baseline, Week 2, and Week 4. Details of the questionnaire items and scoring criteria are provided in Table 2 (McCreight et al., 2018).

**Table 2 T2:** The metformin symptom severity score questionnaire.

No	Question	Option	Score
1	Are you still taking metformin?	Yes (skip to question 6)	0
		No	5
2	If you have stopped taking metformin, was it due to side effects?	Yes (continue to question 3)	5
		No (skip to question 6)	0
3	What dose were you taking at the time of discontinuing metformin?	500 mg once daily (1 tablet)	4
		1,000 mg once daily (2 tablets)	3
		500 mg twice daily (2 tablets)	2
		2,000 mg once daily (4 tablets)	1
		1,000 mg twice daily (2 tablets)	0
4	Have you ever taken a lower dose of metformin and tolerated it well?	Yes	0
		No	1
	If yes, what was the maximum dose you tolerated?	(e.g., 500 mg once daily)	2
5	Have you been trialed on a modified release preparation of metformin (e.g. Glucophage SR)?	Yes	2
		No	0
In the last week of taking metformin, have you experienced?			
6	Nausea?	Yes	1
		No	0
	If yes, how often?	More than once a day	4
		Once a day	3
		Occasionally	2

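### Visit 1 is timed from baseline and not from the last stimulation, so a compliant Week 2 visit can fall 0 to 6 days after a Monday-start course ends, or before the end of a course started on another weekday

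*Protocol article*

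**What the plan says.** Section 2.6.5 of the protocol article refers to Table 1 for the visit windows. The footnote there fixes them: "Baseline = day 0; visit 1 = week 2 (±3 days); visit 2 = week 4 (±3 days". The same section describes "a 1-week baseline period (Week −1 to 0), a 2-week treatment period (Weeks 0–2), and a 2-week follow-up period (Weeks 2–4" weeks.

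Section 2.6.4 ties stimulation to the calendar: "on 5 consecutive weekdays (Monday–Friday) for 2 consecutive weeks". It also says: "All participants will receive two stimulation sessions per day (morning and evening), each lasting 30 min".

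Section 2.5 puts allocation after the baseline measures: "After baseline assessment, a dedicated study coordinator (fully blinded to group assignment) will open envelopes in numerical order". The article prints no weekday for baseline and no maximum interval from baseline to first stimulation.

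For the primary score, section 2.7.2 states: "Assessment time points include baseline, Week 2, and Week 4". The symptom items in Table 2 ask about the last week on metformin, and the stool score in section 2.7.3.1 is a weekly average. Sections 2.7.3.4 and 2.7.3.5 set the cytokines and gut markers at baseline and Week 2.

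**The concern.** The visit and the treatment run on different clocks. The visit is counted from baseline with a symmetric window. The course ends on a day fixed by the calendar and by when stimulation began. Two participants who both comply with Table 1 can therefore be measured at different points relative to the end of treatment, and both readings carry the Week 2 label.

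Three features of this trial make that matter:

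- Section 2.4 gives the pilot's core aim as estimating the SD of the primary score for a later trial. Mixing on-treatment and off-treatment readings under one label can add variance to that SD, and can dilute the effect-size estimates that the abstract promises.
- On sections 2.7.3.4 and 2.7.3.5 and on Table 1, the Week 2 draw is the only post-baseline sample for the cytokines and gut markers. The prose of section 2.6.5 also mentions Week 4 for selected markers, but Table 1 marks none of these there.
- The per-protocol set in section 2.10 requires at least 80% of the course, but not 80% before Visit 1. It does not remove an early reading.

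**Working it through.** **Inputs.** Visit 1 at Week 2 ±3 days with baseline at Day 0 (Table 1 footnote); ten treatment days, Monday–Friday in two consecutive weeks (section 2.6.4); one-week symptom recall (Table 2), taken as the 7 days before the visit for a participant still on metformin.

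**The plan's own figures.** The observation period reproduces: 1 + 2 + 2 = 5 weeks. The plan states no gap between the last stimulation and Visit 1. Its session total does not reproduce: 2 per day × 5 days × 2 weeks = 20, against the total in "on 5 consecutive weekdays (Monday–Friday) for 2 consecutive weeks (total 10 sessions". Those statements must be reconciled. The fractions below count treatment days, so they do not depend on which total is meant.

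**Window.** 14 ± 3 gives Days 11 to 17.

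**Case 1: Day 0 is a Monday and stimulation starts that day.** Treatment days are Days 0–4 and 7–11, so the last is Day 11. Gap = visit day − 11. Recall content = treatment days within (visit day − 7) to (visit day − 1).

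| Visit day | Weekday | Days after last treatment day | Treatment days in recall week |
|---|---|---|---|
| 11 | Fri | 0 | 5 (Days 4, 7–10) |
| 12 | Sat | 1 | 5 |
| 13 | Sun | 2 | 5 |
| 14 | Mon | 3 | 5 (Days 7–11) |
| 15 | Tue | 4 | 4 |
| 16 | Wed | 5 | 3 |
| 17 | Thu | 6 | 2 (Days 10, 11) |

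At Day 11, with two sessions a day, that day's evening session may still be due.

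**Case 2: stimulation starts on Day 0 on another weekday and runs over ten successive weekdays.** The last treatment day is Day 13 for every start from Tuesday to Friday. Treatment days complete before Day 11: Tuesday 9, Wednesday 8, Thursday 7, Friday 7, of 10. A Day 11 visit is 2 days before the end of the course.

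**Case 3 (assumption): the first session waits for the next Monday.** If s is the wait in days, the last treatment day is s + 11.

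| Baseline | s | Last treatment day | Complete before Day 11 | Complete before Day 14 |
|---|---|---|---|---|
| Tue | 6 | 17 | 5/10 | 6/10 |
| Wed | 5 | 16 | 5/10 | 7/10 |
| Thu | 4 | 15 | 5/10 | 8/10 |
| Fri | 3 | 14 | 6/10 | 9/10 |

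**Visit 2.** 28 ± 3 gives Days 25–31. In Case 1 that is 25 − 11 = 14 to 31 − 11 = 20 days after the last treatment day, so the planned two-week follow-up is the minimum and not the centre.

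**The case against.** The best defence is that section 2.6.5 places treatment at Weeks 0–2, directly after the baseline period. Taken with the Monday–Friday rule, that makes Day 0 a Monday with a same-day start, and at least 9 of 10 treatment days are then complete before any in-window visit. Section 2.5 gives an order, baseline then envelope, and no delay. Session scheduling is left to the procedure manual (section 2.6.2), which may fix the start day. A ±3-day window is ordinary, and both arms share it.

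Much of this stands. A reader might infer that Week 2 measures will be taken with only about half the course delivered. The document does not support that as a general statement. It needs a first session about 4 to 6 days after Day 0 (or a full week, for a Monday baseline held over) and a visit at or near the earliest permitted day, and the Weeks 0–2 period speaks against such a lag. For Tuesday and Wednesday baselines, Day 11 is also a Saturday or Sunday. No printed maximum lag excludes the case, but a condensed article may leave that limit to the full protocol, so its absence is not counted here.

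The defence does not remove the core point. The visit window is printed in full in Table 1, and it is counted from baseline. Even on the most favourable reading the gap runs from 0 to 6 days and the recall week holds between 5 and 2 treatment days. The Monday–Friday rule and a Day 0 start both hold strictly only if every baseline is a Monday, and the article does not say so.

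**Conclusion.** The point holds in a limited form. Visit 1 is not anchored to the end of stimulation. With a Monday Day 0 and same-day start, a compliant visit falls 0 to 6 days after the last treatment day. With a Day 0 start on another weekday it can precede the end of the course, with 7 to 9 of 10 treatment days complete before Day 11. A fall to about half depends on the next-Monday assumption and should be treated as conditional.

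The consequence is extra variance and possible dilution in the Week 2 primary score, the stool average and the biomarker draw. It is not directional bias, because the schedule and window are the same in both arms. The document gives no basis for putting a figure on the added variance. The change is worth making because it is cheap and touches the quantity that the pilot is meant to estimate.

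**What to change.** Amend the Table 1 footnote as follows:

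- Define Day 0 as the first stimulation day, and state how long before it the baseline assessment may be.
- Time Visit 1 from the last scheduled session with a one-sided window, never before that session, for example 1 to 5 days after it. Using the scheduled session keeps a window for participants who stop early.
- Time Visit 2 at 14 ±3 days after the last scheduled session, in line with the two-week follow-up in section 2.6.5. Section 2.1 gives a 4-week post-treatment follow-up, and the two must be reconciled first.

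The window needs some width. After a Friday session, 1 to 3 days means Saturday, Sunday and Monday, which is one weekday for fasting outpatient draws. One to 5 days runs to Wednesday and gives three weekdays, with 5, 4 and 3 treatment days in the recall week on Monday, Tuesday and Wednesday.

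The cost is a narrower booking window (for a Monday start, three weekdays against five now: Friday and Monday to Thursday) and possibly a few more window deviations. Section 2.6.3 already has session timing recorded in the CRF, so no new data item is needed.
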